**Methods**

Setting

Mount Sinai Hospital, an academic medical centre with general medicine inpatient units.

Patients

All patients admitted to a general internal medicine ward who survive to hospital discharge home.

Exclusion criteria: Patients who do not have a telephone, patients discharged to a facility (rehabilitation, nursing, other acute care facility), patients who decline to participate.

Study design:

Cluster randomized control trial in a teaching hospital. Clinical teaching unit (CTU) “teams” of patients will be randomized to receive either routine care (no telephone follow up) or intervention (telephone follow up within 72 hrs of discharge). All patients will be followed 30 days after discharge and contacted to collect survey outcome data. Clinical outcomes data will be collected from hospital database.

Survey Design:

Intervention group will receive a phone call within 72 hours after discharge addressing the following domains:

- Patient status since discharge
- Patient’s understanding of discharge instructions
- Patient’s understanding of changes in his/her medications
- Any follow up visits to family practitioner or other specialists
- Any concerns or questions outstanding

All patients will be contacted at 30-days post-discharge to complete a survey regarding outcomes. The survey will contain the Care Transitions Measure-3 (CTM-3), a validated tool to evaluate patients’ perception on coordination of hospital discharge care in addition to questions pertaining to hospital utilization, and rates of adherence to treatment plans and follow up. Follow up surveys may be conducted up to 90 days post discharge.

Callers will follow a standardized script. Patients will be contacted at least five times (unless respondent refuses to participate) to complete the intervention and follow-up survey. Attempts must be made on different days and at different times of the day.

Data Collection

| **Variable** | **Measurement** | **Variable Type** |
| --- | --- | --- |
| *Patient Demographics*  Age  Sex  Admitting diagnosis  Most responsible diagnosis  Family physician  Mean length of stay | Hospital Chart | Continuous  Binary  Categorical  Categorical  Binary  Continuous |

Primary Outcome

Change of 5-points on the Care Transition Measure-3 score (survey)

Secondary Outcomes

30-day Hospital Readmission (TC-LHIN data)

ED visits within 30 days or weeks (TC-LHIN data)

Patient satisfaction (survey)

Adherence to treatment plan (survey)

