Rates of follow up with PCP/outpatient providers (survey)

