**Statistical Analysis**

Sample size justification

A previous study using the CTM-3 in a similar patient population found a mean of 80.3% with a standard deviation of 19.6.^4^ We determined that a 7-point absolute difference in CTM-3 scores would be clinically relevant to physicians and hospital administrators. With an alpha-error of 0.05 (2-sided) and a beta-error of 0.20 (1-sided), the unadjusted total sample needed to detect a 7-point difference in CTM-3 scores was 95 in each arm. Assuming a 50% response rate of patients completing the post-discharge survey, we calculated an adjusted sample size of 190 in each arm, or 380 patients in total. Given that over an average month, 254 patients are discharged from the GIM service at our hospital and assuming a conservative historical trend of 80% of patients returning home and a 50% participation rate, we elected to conduct the study over a 4-month period.

Descriptive analyses will be used to summarize results (e.g., means, medians, and standard deviations). Continuous variables will be compared using Mann-Whitney test and categorical variables with Fisher’s exact test or Chi-square.

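### Whole teams are randomized and case-mix variables are collected, but the planned arm comparisons are unadjusted two-group tests, so measured imbalance between teams goes uncorrected

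*Protocol*

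**What the plan says.** The protocol's Methods, under Study design, describe a "Cluster randomized control trial in a teaching hospital" in which clinical teaching unit teams are allocated to the call or to routine care. The number of teams is not given, and no stratification or matching of teams is described.

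The Data Collection table in Methods lists the chart variables "Age Sex Admitting diagnosis Most responsible diagnosis Family physician Mean length of stay". Family physician is recorded as a binary variable. CTM-3 is measured after discharge, so it has no baseline value.

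The outcomes are the CTM-3 score, 30-day readmission, ED visits, satisfaction, adherence and "Rates of follow up with PCP/outpatient providers (survey".

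The Statistical Analysis section promises descriptive summaries and then names the tests: "Continuous variables will be compared using Mann-Whitney test and categorical variables with" Fisher's exact or chi-square. It mentions no regression model, covariate or team term.

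**The concern.** Randomizing patients balances case mix across hundreds of units. Randomizing teams within one hospital balances it only across as many units as there are teams. If teams differ in age, diagnosis or the share of patients with a family physician, that difference appears in the arm comparison and can be read as an effect of the call. Mann-Whitney, Fisher's exact and chi-square tests cannot remove it, although the chart data needed to do so are already being collected.

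Follow-up with outpatient providers is the plainest case, because having a family physician makes one route to that outcome easier. Readmission, ED visits and CTM-3 are exposed to whatever extent they depend on case mix. A second, smaller cost is that any CTM-3 variance the covariates explain stays in the error term.

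**Working it through.** **1. The plan's own figure.** Inputs from the Statistical Analysis section: SD 19.6, difference 7 points, two-sided alpha 0.05, power 0.80.

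n per arm = 2 × (1.960 + 0.842)² × 19.6² / 7² = 123.1, so 124. The protocol states 95, which these inputs do not reproduce. At 95 per arm, power = Φ(7 / (19.6 × √(2/95)) − 1.96) = Φ(2.461 − 1.960) = 69.2%. That mismatch is a separate matter; it matters here because 69%, not 80%, is the baseline for any precision gain.

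**2. Chance imbalance in family physician status.** From the Statistical Analysis section, expected participants = 254 × 0.80 × 0.50 × 4 = 406. Assumed, because the protocol gives no figures: 25% without a family physician, equal arms and equal team sizes, 4 to 16 teams in total, ICC of that variable 0.01 to 0.05.

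SE = √(4 × 0.25 × 0.75 / 406 × DE), with design effect DE = 1 + (406/teams − 1) × ICC.

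Under patient-level randomization DE = 1 and SE = 4.3 percentage points. Under team allocation, SE in percentage points:

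| Teams in total | ICC 0.01 | ICC 0.02 | ICC 0.05 |
|---|---|---|---|
| 4 | 6.1 | 7.5 | 10.5 |
| 8 | 5.3 | 6.1 | 8.0 |
| 16 | 4.8 | 5.2 | 6.4 |

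Worked corner: 4 teams, ICC 0.05 gives DE = 1 + 100.5 × 0.05 = 6.0 and SE = 4.3 × √6.0 = 10.5.

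**3. What an imbalance does to an outcome.** Illustration only: suppose follow-up rates differ by 40 points between patients with and without a family physician. An imbalance of one SE then shifts the raw arm difference by 0.40 × 4.8 = 1.9 to 0.40 × 10.5 = 4.2 points with no effect of the call. If follow-up rates differ by 20 points, the shift is half that.

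**4. Precision for CTM-3.** Residual SD = 19.6 × √(1 − R²). R² is assumed, since the protocol gives no association between the covariates and CTM-3. Power for 7 points at 95 per arm, ignoring clustering:

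| R² | Residual SD | Power |
|---|---|---|
| 0 | 19.60 | 69.2% |
| 0.02 | 19.40 | 70.1% |
| 0.05 | 19.10 | 71.4% |
| 0.10 | 18.59 | 73.7% |
| 0.15 | 18.07 | 76.1% |

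An R² of about 0.23 would be needed for 95 per arm to reach 80%.

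**5. Why covariates alone are not enough.** With 190 CTM-3 completers in 4 to 16 teams and an assumed outcome ICC of 0.01 to 0.05, DE = 1 + (190/teams − 1) × ICC runs from 1.11 (16 teams, 0.01) to 3.33 (4 teams, 0.05). A patient-level test at a nominal 5% then has a real type I error of 2 × (1 − Φ(1.96/√DE)), about 6% to 28%. Adding patient covariates without a team term leaves the standard errors too small.

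**The case against.** The best defence is that covariate lists and adjusted models are commonly left to a statistical analysis plan, which may exist but is not shown, and that an unadjusted comparison is not wrong in itself. The first part has limited force: the protocol does not leave the method open but names its tests, and a later adjusted main analysis would depart from them. The second part would carry more weight if patients were randomized; with whole teams allocated, raw comparisons are more exposed to case mix.

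It can also be said that the Statistical Analysis wording covers continuous and categorical variables in general, so the chart variables may be compared between arms. That is a fair reading, but such a comparison would show an imbalance without correcting it.

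Three stronger readings are tempting, and the document does not support them:

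- A reader might infer that worthwhile precision is being given away at no cost. No R² is given and no baseline CTM-3 exists. The gain is about 1 to 7 power points over the assumed range, and a many-level diagnosis factor is costly with few teams.
- A reader might infer that a 10-point imbalance is to be expected. That is the SE at the high end of the assumptions; other combinations give about 5 to 8.
- A reader might infer that family physician status nearly determines the follow-up outcome. That outcome also counts other outpatient providers, so a patient without a family physician can meet it.

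What stands in full is that adjustment corrects only measured imbalance. Differences between teams in discharge practice would remain, and ordinary regression on arm and patient covariates would keep the clustering error.

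**Conclusion.** The point holds as a weakness in a stated method. The protocol allocates teams, collects usable pre-allocation covariates and commits to tests that cannot use them. Under the assumptions in the working, team allocation raises the SE of the between-arm difference in the share without a family physician from 4.3 to about 5 to 10.5 points. With 16 teams and an ICC of 0.01 the increase is slight; with 4 teams and an ICC of 0.05 it is more than double. The size therefore depends on two quantities the protocol does not state.

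The case rests mainly on imbalance. The CTM-3 power gain (69% to 70–76% for an assumed R² of 0.02 to 0.15) is a lesser benefit, is calculated ignoring clustering, and would not restore the planned 80%. The change is worth making, provided the replacement model accounts for team.

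**What to change.** Replace the two-group tests as the main analysis with a prespecified model that accounts for team: a mixed model or GEE with a small-sample correction, or a two-stage cluster-level analysis. Choose among them once the number of teams is stated.

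- Adjust for a short list settled before a patient comes under an allocated team: age, sex and family physician (yes/no). Add a coarse grouping of admitting diagnosis only if the number of teams allows.
- Use the matching binary model for readmission, ED visits and follow-up, with the same covariates.
- Keep an unadjusted comparison as supporting, also cluster-aware.
- Confine length of stay and "Most responsible diagnosis" to a sensitivity model, because both are settled after the patient is under an allocated team.

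The cost is revised analysis wording, a few degrees of freedom and a little more analysis work; no new data are needed. The protocol should also say that adjustment addresses measured imbalance only. With very few teams the limits are severe whatever the covariates: a cluster-level comparison of 4 teams has 4 − 2 = 2 degrees of freedom.

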**Budget Justification**

As the proposed study is part of a quality improvement initiative, members of current medical care teams will be required to perform the post-discharge phone calls as a matter of routine care. Funding application has been put forth to the Office of Patient Experience and Outcomes at Mount Sinai Hospital to facilitate the cost of a research coordinator (0.5 FTE) to track the patients enrolled and to conduct follow-up telephone surveys.

